## Appendix 2. Investigator survey

#### (Leeds Dyspepsia Questionnaire, LDQ)

| 1 | Over the last FOUR WEEKS have you had any **indigestion** (a pain in the upper abdomen) (see picture)?  YES [ ] NO [ ]  *If the answer is no please go to question 2.*  How severe has your indigestion been over the last FOUR WEEKS?  Very mild [ ] Mild [ ] Moderate [ ] Severe [ ]  Very severe [ ] | [figure not shown] |
| --- | --- | --- |
|  |  | epigastric pain, discomfort, or burning.  * Note the difference in location from #2! |
| 2 | Over the last FOUR WEEKS have you experienced heartburn (a burning feeling behind the breast bone) (see picture)?  YES [ ] NO [ ]  *If the answer is no please go to question 3.*  How severe has your heartburn been over the last FOUR WEEKS?  Very mild [ ] Mild [ ] Moderate [ ] Severe [ ]  Very severe [ ] | [figure not shown] |
|  |  | Chest burning, discomfort, or pain. |
| 3 | Over the last FOUR WEEKS has **food or drink ever stuck behind your breast bone as it went down**?  YES [ ] NO [ ]  *If the answer is no please go to question 4.*  How severe has your symptom been over the last FOUR WEEKS?  Very mild [ ] Mild [ ] Moderate [ ] Severe [ ]  Very severe [ ] | Chest discomfort or pain when swallowing, odynophagia (ddx) or dysphagia. |
| 4 | Over the last FOUR WEEKS have you experienced any **regurgitation** (an acid taste coming up into your mouth from your stomach)?  YES [ ] NO [ ]  *If the answer is no please go to question 5.*  How severe has your regurgitation been over the last FOUR WEEKS?  Very mild [ ] Mild [ ] Moderate [ ] Severe [ ]  Very severe [ ] | Reflux of gastric contents (reflux) (ddx) belching, vomiting, or rumination. |

| 5 | Over the last FOUR WEEKS have you noticed excessive **burping or belching**?  YES [ ] NO [ ]  *If the answer is no please go to question 6.*  How severe has your belching been over the last FOUR WEEKS?  Very mild [ ] Mild [ ] Moderate [ ] Severe [ ]  Very severe [ ] | Belching, oral expulsion of gas only. |
| --- | --- | --- |
| 6 | Over the last FOUR WEEKS have you experienced any **nausea** (a feeling of sickness without actually being sick)?  YES [ ] NO [ ]  *If the answer is no please go to question 7.*  How severe has your nausea been over the last FOUR WEEKS?  Very mild [ ]  Mild [ ] Moderate [ ]  Severe [ ]  Very severe [ ] | Nausea, retching. |
| 7 | Over the last FOUR WEEKS have you experienced any **vomiting**?  YES [ ] NO [ ]  *If the answer is no please go to question 8.*  How severe has your vomiting been over the last FOUR WEEKS?  Very mild [ ] Mild [ ] Moderate [ ] Severe [ ]  Very severe [ ] | Accompanied by nausea or retching (ddx) reflux, rumination, belching. |
| 8 | Over the last FOUR WEEKS have you noticed an  **excessive feeling of fullness after eating**?  YES [ ] NO [ ]  *If the answer is no please go to question 9.*  How severe has your fullness been over the last FOUR WEEKS?  Very mild [ ] Mild [ ] Moderate [ ] Severe [ ]  Very severe [ ] | Post-prandial fullness, incorrect sensation of fullness. |
| 9 | Which, if any, of these symptoms has been the most troublesome to you over the last FOUR WEEKS?  TICK ONE BOX ONLY   1. Heartburn [ ] 2. Regurgitation [ ] 3. Indigestion [ ] 4. Belching [ ] 5. Nausea [ ] 6. Vomiting [ ] 7. Excessive fullness [ ] 8. None of these has troubled me [ ] |  |

## Appendix 3. Subject survey

| S |  |  |  |  |  |
| --- | --- | --- | --- | --- | --- |
|  |  | - |  |  |  |
|  |  |  |  |  |  |

| **Protocol number** | **Naxozol_P4_1** | | | | | | | | | | | | |
| --- | --- | --- | --- | --- | --- | --- | --- | --- | --- | --- | --- | --- | --- |
| **Screening number** |  | | | | | | | | | | | | |
| **Randomization number** |  | | | | | | | | | | | | |
|  |  | **R** |  | | |  | |  | |  | |  |  |
|  |  |  |  |  |  | - | |  |  |  |  |  |  |
|  |  |  |  | | |  | |  | |  | |  |  |
| **Subject initials** |  | | | | | | | | | | | | |
|  |  | | |  | | |  | |  | |  | | |
|  |  |  |  |  | | |  | |  | |  |  |  |
| **Date of visit** | **Visit 2** | | | | YY MM DD | | | | | | | | |
|  | **Visit 3** | | | |  |  |  |  |  |  |  |  |  |
| **Investigator** |  | | | | | | | | | | | | |

- - Thank you very much for participating in our clinical trial.
  - The information provided on this form will not be used for purposes other than this study.
  - Please fill out the form as accurately and credibly as possible.
  - Please return this form after completion.
  - Thank you again for participating in this study.

**Pain (VAS)**

| Protocol number | Visit | Screening number | | | | Randomization number | | | | Initials |
| --- | --- | --- | --- | --- | --- | --- | --- | --- | --- | --- |
| Naxozol_P4_1 |  | S |  |  |  | R |  |  |  |  |

Please indicate your pain level by drawing a line across the straight line below (VAS):

**(Pain VAS)**

| **No pain** |  | **Worst pain imaginable** |
| --- | --- | --- |
|  |  |  |

#### Gastrointestinal Symptom Rating Scale (GSRS)

Please read the following and check the number that corresponds to your experience over the past 3 months.

- 1.
[figure not shown]

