## Drugs or therapies contraindicated prior to study participation

Subjects who received the following medications for the periods listed below cannot participate in the study:

1. NSAIDs (LDA [≤325 mg / day low dose aspirin] excluded) within 7 days prior to administration of the investigational product.
2. Gastroprotective agents (including H2 blockers, PPIs, misoprostol, etc.) within 7 days prior to administration of the investigational product.
3. IV or oral corticosteroids (oral corticosteroids corresponding to ≤7.5 mg / day prednisone, topical ointments, eyedrops, and nasal agents are excluded) within 7 days prior to investigational product administration.
4. Intraarticular or intramuscular corticosteroids or hyaluronic acid within 8 weeks prior to administration of the investigational product.
5. Glucosamine and / or chondroitin sulfate within 7 days prior to administration of the investigational product.
6. Lithium within 7 days prior to administration of the investigational product.
7. Antiretrovirals (atazanavir, atazanavir sulfate) within 7 days prior to administration of the investigational product.

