## Evaluation schedule

A general summary of the study procedure is shown in the study flow chart (Appendix 1). All visits must be conducted according to the pre-determined schedule. The study duration for each subject is 12-14 weeks and consists of the following evaluations:

- - Screening and washout period: 0 - 2 weeks (Day -14 - Day 1).
  - Treatment & F/U period: 12 weeks (Day 1 - Day 84).

The visit schedule during the study consists of 3 visits, including 1 pre-treatment screening visit. Randomization and study drug distribution will be conducted at visit 2, and the last visit will be conducted 12 weeks after the first day of the investigational product administration.

Additional visits may be conducted if adverse events occur.

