#### Early termination visit

During this visit, the following procedures and evaluations will be conducted, as per visit 3:

- - Record the reason for early termination.
  - Record all new adverse events and / or changes in pre-existing adverse events.
  - Record all co-administered drugs and / or changes in pre-existing co-administered drugs.
  - Conduct the pain VAS evaluation.
  - Conduct the LDQ evaluation.
  - Distribute the GSRS and EQ-5D surveys and ask the subjects to answer them.
  - Physical examination.
  - Vital signs (blood pressure, pulse rate, respiratory rate).
  - Blood sample collection.
  - Collect the unused investigational products, ancillary drugs, and rescue drugs.
  - Collect the completed subject log.
  - Complete the case report form.

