## Secondary outcome analysis

- The average LDQ after 12 weeks of oral administration of the investigational product: descriptive statistics (sample size, mean, standard deviation, median, min, max) will be presented for the LDQ score after 12 weeks of investigational product administration. The between-group difference will be tested for significance using the independent two-sample t-test or the Wilcoxon rank sum test.
- The average change in the GSRS from baseline after 12 weeks of oral administration of the investigational product: descriptive statistics (sample size, mean, standard deviation, median, min, max) will be presented for GSRS measured before and after 12 weeks of investigational product administration, and the change in GSRS from baseline after 12 weeks of oral administration of the investigational product in each treatment arm. The change within each arm will be tested for significance using the paired t-test or the Wilcoxon signed rank test. The between-group difference at each time point and in the amount of change will be tested for significance using the independent two-sample t-test or the Wilcoxon rank sum test.
- The incidence rate of GI adverse events (dyspepsia, diarrhea, nausea, abdominal pain, heartburn) after 12 weeks of oral administration of the investigational product: the number and proportion of the subjects who experience a GI adverse event during the 12 weeks of investigational product administration, and the frequency of these events, will be presented for each treatment arm. The between-group difference in proportion will be tested for significance using the Chi-square test or Fisher’s exact test.
- The discontinuation rate due to GI adverse events after 12 weeks of oral administration of the investigational product: the number and proportion of subjects who discontinue drug administration due to GI adverse events that occur during the 12 weeks of investigational product administration will be presented for each treatment arm. The between-group difference in proportion will be tested for significance using the Chi-square test or Fisher’s exact test.

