# Appendices

## Appendix 1. Study schedule

| Schedule | Screening & Washout period | | Treatment & Follow-up Period* | |
| --- | --- | --- | --- | --- |
|  | Screening1 | Randomization | | End of Study |
| Weeks | -2 - 0 | 0 | | 12 |
| Day of visit | -14 - 1 | 1 | | 84-87 |
| Visit category | V1 | V2 | | V3 |
| Consent |  |  | |  |
| Screening number assignment |  |  | |  |
| Inclusion / exclusion criteria |  |  | |  |
| Demographic information / medical history / medication history |  |  | |  |
| Physical examination 2 | (including weight) |  | |  |
| Vital signs3 |  |  | |  |
| X-ray (lesion)4 |  |  | |  |
| Pain VAS5 | - |  | |  |
| Randomization |  |  | |  |
| Blood test |  |  | |  |
| Blood chemistry test 6 |  |  | |  |
| Hematological test 7 |  |  | |  |
| Pregnancy test8 |  |  | |  |
| Drug administration |  |  | |  |
| Distribution of study drug / ancillary drug / rescue drug |  |  | |  |
| Collection of study drug / ancillary drug / rescue drug |  |  | |  |
| LDQ, GSRS, EQ-5D |  |  | |  |
| Distribution of subject log |  |  | |  |
| Collection of subject log |  |  | |  |
| Confirmation of co-administered drugs |  |  | |  |
| Adverse event monitoring |  |  | |  |

1. If additional washout is not needed, screening and randomization can be conducted on Day 1.
2. Height (history), weight (measured). Weight measured only at visit 1.
3. Blood pressure, pulse rate, respiration rate.
4. Not conducted if there is an X-ray result of the lesion taken within 6 months.
5. Conducted only at visit 2 and not at visit 1.
6. ALT, AST, BUN, creatinine, glucose, total bilirubin.
7. CBC (hemoglobin, hematocrit, RBC count, WBC with differential count, platelet count).
8. Conducted only in women of childbearing potential.

- **Additional visit**: Additional visits may be conducted if follow-up observation of adverse events is needed.

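### The GSRS form's 3-month recall does not fit the visit schedule, so baseline and early-termination scores largely describe time before trial treatment

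*Protocol*

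**What the plan says.** Appendix 3 prints the recall period on the subject's GSRS form: "Please read the following and check the number that corresponds to your experience over the past 3 months". Section 6.1 has the form completed at Visit 2 (Day 1) and Visit 3, and gives the same instruction for the early termination visit: "Distribute the GSRS and EQ-5D surveys and ask the subjects to answer them".

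The periods around those visits, from Section 6.1, are "Screening and washout period: 0 - 2 weeks (Day -14 - Day 1") and "Treatment & F/U period: 12 weeks (Day 1 - Day 84"). Appendix 1, note 1 adds: "If additional washout is not needed, screening and randomization can be conducted on Day 1". Section 5.3.2 bars NSAIDs (low-dose aspirin aside) and gastroprotective agents "within 7 days prior to administration of the investigational product". Visit 3 falls on Day 84±7 in the Synopsis and on Day 84–87 in Section 6.1.

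The GSRS comparison is the first secondary objective in Section 3. Section 7.3.2 defines the endpoint as a change from baseline after 12 weeks, and Section 7.5.3 analyses "The average change in the GSRS from baseline after 12 weeks of oral administration of the investigational product" with a paired test within each arm and a two-sample test between arms.

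The LDQ in Appendix 2, the other upper-GI symptom scale in the trial, uses a shorter period, for example "How severe has your indigestion been over the last FOUR WEEKS". Section 6.4.2 describes the GSRS without mentioning recall, and nothing in the protocol explains the 3-month choice.

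**The concern.** A change score is interpretable when the first rating describes the state before treatment and the second the state the endpoint names. A 3-month window strains both.

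On Day 1 it reaches back well past any washout. For subjects who had been taking an NSAID or a gastroprotective agent, the baseline then records mostly how they felt on that earlier drug. The within-arm paired tests would be contrasting earlier therapy with trial therapy, although a reader will take them as change from an untreated state.

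At Visit 3 the window is slightly longer than the exposure. It pools early and late treatment with a few days before the first dose, whereas the endpoint wording points to the state after 12 weeks. At early termination most of the window can lie before the first dose.

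The two symptom scales also describe different periods, which makes the GSRS a weaker cross-check on the LDQ. Because the recall period is printed on the form, no later analysis document can recover the intended one.

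**Working it through.** **Inputs.** Treatment Day 1 to Day 84 and screening/washout 0–2 weeks (Section 6.1); 7-day bar on prior NSAIDs and gastroprotective agents (Section 5.3.2); Visit 3 windows (Synopsis, Section 6.1); LDQ recall 4 weeks = 28 days (Appendix 2). The protocol gives no day count for 3 months. I assume 91 days and show 89–92 as the range. A visit on Day d has d − 1 days elapsed since Day 1. The shares count calendar days and assume that each recalled day weighs equally.

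**The plan's own figure.** The protocol gives no calculation for the GSRS. Its one computed figure is the LDQ sample size, which reproduces: 2 × 0.65² × (1.96 + 0.842)² / 0.4² = 41.46, rounded up to 42 per arm; 42 / 0.8 = 52.5, rounded up to 53. GSRS recall does not enter it.

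**Visit 2, subjects coming off a barred drug.** Share before washout = (recall − washout days) / recall.
- 14-day washout: (91 − 14)/91 = 77/91 = 85% (84–85% over 89–92 days).
- 7-day washout: (91 − 7)/91 = 84/91 = 92% (92% over the range).

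**Visit 3.** Pre-dose share = (recall − (d − 1)) / recall, floored at zero.

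| Visit day | Days elapsed | Pre-dose share, 91 days | Range, 89–92 days |
|---|---|---|---|
| 77 | 76 | 15/91 = 16% | 13/89 = 15% to 16/92 = 17% |
| 84 | 83 | 8/91 = 9% | 6/89 = 7% to 9/92 = 10% |
| 87 | 86 | 5/91 = 5% | 3/89 = 3% to 6/92 = 7% |
| 91 | 90 | 1/91 = 1% | 0 to 2/92 = 2% |

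Across both visit windows, about 83–100% of the recalled days are on treatment. If pre-dose symptoms are equal in expectation between arms, the between-arm difference in completers is diluted by about 0–17%.

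**Early termination.** The same formula gives Day 8: 84/91 = 92%; Day 15: 77/91 = 85%; Day 29: 63/91 = 69%; Day 43: 49/91 = 54%. The share passes one half when 45.5 days have elapsed, at about Day 46.

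**With a four-week recall.** Even at Day 77, 76 days have elapsed, more than 28, so the Visit 3 window holds no pre-dose days. At Visit 2 the share before washout would be (28 − 14)/28 = 50% or (28 − 7)/28 = 75%.

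**The case against.** The best defence is that the objective in Section 3 compares the two arms over 12 weeks of treatment, and a 3-month recall at Visit 3 nearly coincides with that period. Both arms answer the same form, and randomization balances the baseline contamination in expectation, so the between-arm difference in change is not biased by it. This stands. A reader might infer that the GSRS cannot measure the effect of 12 weeks of treatment at all; the figures above do not support that for completers.

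Nor does every subject wash out. The period is 0–2 weeks, and screening and randomization can share a day. The 85–92% matters only for subjects recently on an NSAID or gastroprotective agent, and the protocol does not give their share. This also stands. It does not clear everyone randomized on the screening day: someone who stopped such a drug just over a week earlier needs no further washout, yet still rates the months on it.

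Two stronger readings should be set aside. One is that dilution favours a finding of non-inferiority. Non-inferiority is tested on LDQ change alone (Section 7.5.2); the GSRS gets a two-sided 5% test, so dilution costs power on a secondary comparison. The other is that early-termination scores will serve as week-12 values. Section 6.1 only requires that they be collected, Section 7.5.1 plans multiple imputation for missing data, and assigning early visits to analysis time points is commonly left to the SAP.

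Finally, a four-week recall does not clean the baseline. That is true, and it limits what the fix can claim.

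**Conclusion.** The mismatch is real and confined to one secondary scale. It bears most on the baseline of subjects coming off an NSAID or gastroprotective agent, hence on the within-arm paired tests, and on any score collected at early termination before about Day 46. For completers at Visit 3 the effect is modest: the score is a whole-course average with a small pre-dose share instead of the state after 12 weeks, and the randomized comparison remains valid with some dilution. The primary LDQ analysis is unaffected, since GSRS recall plays no part in it and the LDQ's own four-week window lies wholly within treatment at Visit 3. The sample size is likewise unaffected.

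These sizes rest on reading 3 months as 89–92 days and on equal weighting of recalled days. The effect on any estimate cannot be computed from the protocol, which gives neither the proportion of subjects with recent prior therapy nor the symptom levels on it.

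**What to change.** In Appendix 3, change the GSRS recall from three months to the last four weeks, the period used for the LDQ in Appendix 2, at Visit 2, Visit 3 and early termination. The Visit 3 window then lies wholly within treatment, both scales cover the same period, and the pre-washout share of baseline falls from 85–92% to 50–75%.

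Because that share remains large, Section 7.5.3 should say that within-arm GSRS change is descriptive and will not be presented as a treatment effect; the between-arm comparison carries the inference. If the 3-month form has to be kept, Section 7.3.2 should instead define the endpoint as average symptoms over the treatment period.

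The cost is one line on a questionnaire and one sentence in the analysis section, with no added visits or data. The downside is less comparability with earlier use of the 3-month form.

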**Abdominal pain**

This means pain in the entire area of the abdomen (below the ribs, not in the chest).

[0]. No pain, or momentary pain.

[1]. Pain or discomfort that occurs intermittently and hinders activity.

[2]. Prolonged pain or discomfort that required alleviation and hinders many social activities.

[3]. Severe and debilitating pain that affects all social activities.

#### Heartburn

[figure not shown]
This means burning pain in the esophagus area (post-sternal).

[0]. No burning, or momentary burning.

[1]. Short-term discomfort that occurs intermittently.

[2]. Prolonged discomfort that occurs often and requires alleviation.

[3]. Prolonged discomfort that is temporarily alleviated by antacids.

#### Acid regurgitation

This means unpleasant reflux of acidic fluid from the stomach towards the chest.

[0]. No regurgitation, or momentary regurgitation.

[1]. Bothersome regurgitation that occurs intermittently.

[2]. Regurgitation that occurs 1-2 times a day and requires alleviation.

[3]. Regurgitation that occurs many times a day and is only temporarily and ineffectively alleviated by antacids.

#### Burning sensation in the epigastrium

[figure not shown]
This means a burning sensation in the middle of the upper abdomen.

[0]. No burning sensation, or momentary sensation.

[1]. Short-term discomfort that occurs intermittently; no antacids or food needed between meals.

[2]. Prolonged discomfort that occurs frequently and requires food or antacids between meals.

[3]. Prolonged discomfort that often requires food or antacids between meals.

#### Nausea and vomiting

[0]. No nausea.

[1]. Short-term nausea that occurs intermittently.

[2]. Prolonged nausea that occurs frequently without vomiting.

[3]. Continuous nausea with frequent vomiting.

#### Borborygmus

This means a gurgling sound in the abdomen.

[0]. No borborygmus or intermittent borborygmi.

[1]. Bothersome, short-term borborygmi that occur intermittently.

[2]. Prolonged, frequent borborygmi that are inhibited by movement and do not hinder social activities.

[3]. Continuous borborygmi that severely hinder social activities.

#### Abdominal distension

This means fullness, a feeling of indigestion, and flatulence.

[0]. No distension, or momentary distension.

[1]. Short-term discomfort that occurs intermittently.

[2]. Prolonged discomfort that occurs frequently and can be increased by tight-fitting clothes.

[3]. Continuous discomfort that severely hinders social activities.

#### Eructation

This is expulsion of gas through the mouth without rumination, which is regurgitation of gastric contents, and vomiting.

[0]. No eructation, or momentary eructation.

[1]. Bothersome eructation that occurs intermittently.

[2]. Frequent eructation that hinders some social activities.

[3]. Frequent eructation that severely hinders social activities.

#### (EQ-5D)

Please read the following and check the number that best corresponds to your status.

1. **Exercise**
2. I have no issues with walking.
3. I have some issues with walking.
4. .I need to sit / lie down all the time.

#### Self-care

1. I have no issues with bathing or dressing.
2. I have some issues with bathing or dressing.
3. I cannot bathe or dress by myself.

#### Daily activities (work, study, housework, family, leisure)

1. I have no issues with daily activities.
2. I have some issues with daily activities.
3. I cannot perform daily activities.

#### Pain / discomfort

1. I do not have pain or discomfort.
2. I have moderate pain or discomfort.
3. I have severe pain or discomfort.

#### Anxiety / depression

1. I am neither anxious nor depressed.
2. I am somewhat anxious or depressed.
3. I am severely anxious or depressed.

####
[figure not shown]
How would you rate your overall health status?

Very bad Very good

